##### Cognitive distortions

Cognitive distortions of the juvenile will be measured using case-file analysis at T1 and T2 of the Brief Irrational Thoughts Inventory (BITI) [57]. The BITI is filled out by juveniles as part of the standard FAST procedure and contains three subscales: Aggression and Justification (nine items), Sub-assertiveness (five items), and Distrust (four items). All items are rated on a 6-point Likert scale ranging from 1 = *totally disagree* to 6 = *totally agree*.

#### Moderators

##### Demographics

Participant demographics will be obtained at T1 using a questionnaire about demographic information. The demographics questionnaire contains nine items for juveniles, 19 items for caregivers, and eight items for therapists. The items measure gender, age, and ethnicity for all respondents. Additionally, for juveniles and caregivers, family composition is measured. For caregivers, work, and financial situation are measured. For therapists, educational degrees and work experience are measured.

##### Juvenile and caregiver psychopathology

Psychopathology of the juvenile will be measured at T1 using juvenile and caregiver report on the Inventory of Callous-Unemotional Traits (ICU) [58] and on the Narcissism (seven items) and Impulse control (five items) scales of the Antisocial Processes Screening Device (APSD) [59]. In addition, primary diagnoses of the juvenile are retrieved from case files. Psychopathology of the caregiver will be measured at T1 using case file analysis of the RAF GGZ Youth [39]. The ICU contains 24 items, which are rated on a 4-point Likert scale ranging from 0 = *not at all true* to 3 = *definitely true*. Items on the APSD are rated on a 3-point Likert scale ranging from 1 = *definitely not true* to 3 = *definitely true*. The RAF GGZ Youth contains one items asking therapists whether caregiver psychopathology is present. The item is rated on a 3-point Likert scale ranging from 0 = *not present* to 2 = *clearly present*.

##### Social support

See the description on Social Support in the section Mechanisms of Change.

##### Treatment characteristics

The following treatment characteristics will be assessed: treatment integrity, including adherence to the assigned level of online therapy, treatment duration, intensity and completion, therapist-client alliance, motivation, expectancies, and cooperation.

Treatment integrity will be measured at T2 using the FAST evaluation form, which is filled out separately by juveniles, caregivers, and therapists as part of the standard FAST procedure. The FAST evaluation form assesses whether the working elements of FAST were sufficiently applied during treatment (i.e., juveniles and caregivers report whether treatment goals were set in collaboration with them and therapists report whether they made sufficient use of cognitive behavioral therapy techniques) and whether treatment duration and appointment frequency matched the recidivism risk level. Treatment integrity will be scored in percentages, where a higher percentage indicates higher treatment integrity.

Adherence to the assigned level of online therapy within FASTb and FASTr will be measured at T2 by calculating the average percentage of online and face-to-face direct treatment time over the duration of intervention in two ways. First, it will be calculated based on registered direct time by therapists in their appointment agendas. Registration codes indicate whether the direct treatment time was online or face-to-face. In addition, caregivers will be asked monthly to report how many online appointments and how many face-to-face appointments they have had with their therapist in the past month. At T2, the average percentage of online and face-to-face appointments over the duration of the intervention will be calculated based on both measures.

Treatment duration, intensity, and completion will be assessed using case file analysis. Duration and intensity will be calculated based on the registered direct treatment time by therapists in their appointment agendas. Treatment duration will be measured in weeks and treatment intensity will be measured in average hours of direct treatment time per week. Treatment completion will be assessed by coding whether FAST completion was registered as positive or negative.

Therapist-client alliance will be measured at T2 using juvenile and caregiver report on the Relationship with Interventionist [60]. The Relationship with Interventionist contains 12 items, which are rated on a 6-point Likert scale ranging from 1 = *totally disagree* to 6 = *totally agree*.

Treatment motivation of juveniles and caregivers will be measured at T1 and T2 using self-report on the Treatment Motivation Scales for Forensic Outpatient Treatment (TMS-F) [61]. The TMS-F contains 16 items, which are rated on a 5-point Likert scale ranging from 1 = *totally disagree* to 5 = *totally agree*.

Treatment expectancies will be measured at T1 using caregiver report on the Parent Expectancies of Therapy Scale (PETS) [62, 63], and therapist report at T1 and T2 on one item asking how effective they think the assigned version of FAST (FASTb or FASTr) is in comparison to the other version of FAST. Therapists rate the question on a 5-point Likert scale ranging from 1 = *much less effective* to 5 = *much more effective*. The PETS contains seven items, which are rated on a 5-point Likert scale ranging from 1 = *low expectations* to 5 = *high expectations*.

Treatment cooperation will be measured at T2 using juvenile, caregiver, and therapist report on the Cooperation Scale [60]. The Cooperation Scale contains five items, which are rated on a 6-point Likert scale ranging from 1 = *totally disagree* to 6 = *totally agree*.

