## Abstract

**Background:**

Antisocial behavior during adolescence can have long-lasting negative effects and leads to high societal costs. Forensic Outpatient Systemic Therapy (Forensische Ambulante Systeem Therapie; FAST) is a promising treatment for juveniles aged 12–21 showing severe antisocial behavior. The intensity, content and duration of FAST can be adjusted to the needs of the juvenile and their caregiver(s), which is considered crucial for effective treatment. Next to the regular version of FAST (FASTr), a blended version (FASTb) in which face-to-face contacts are replaced by minimally 50% online contacts over the duration of intervention was developed during the Covid-19 pandemic. The current study will investigate whether FASTb is equally effective as FASTr, and through which mechanisms of change, for whom, and under which conditions FASTr and FASTb work.

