#### FASTr-condition

FASTr includes around 3 hours of face-to-face direct treatment time weekly. It consists of a maximum of 10% online direct treatment time, i.e., treatment via phone, video-calling or texting.

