#### FASTb-condition

FASTb consists of a minimum average of 50% online direct treatment time over the duration of the intervention, such as phone calls, video calls, text messages, and eHealth. For more information on differences between FASTr and FASTb, see Table 2. eHealth involves the use of the software platform Minddistrict and the GRIP-app, a simple app which is combined with a heart rate watch on the client’s mobile telephone that registers physiological aspects of stress and anger and warns clients when they get aroused.

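### The T2 adherence score is written as a percentage of appointments, while both arms, and the opening of the same paragraph, use a percentage of treatment time

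*Protocol article*

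**What the plan says.** Both arms are defined in units of time. Under *FASTb-condition* the blended arm has "a minimum average of 50% online direct treatment time over the duration of the intervention", and eHealth is listed there among the online components. The Background section on blended care gives the same definition. Under *FASTr-condition* the regular arm is limited: "It consists of a maximum of 10% online direct treatment time, i.e., treatment via phone, video-calling or texting". The Abstract words the blended arm differently: "face-to-face contacts are replaced by minimally 50% online contacts".

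Adherence to the assigned online share is described under *Treatment characteristics*, in the Moderators part of Measures. The paragraph first says that a percentage of direct treatment time will be calculated in two ways:

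- The first uses the direct time that therapists register in their agendas, with codes for online or face-to-face.
- The second asks caregivers each month to "report how many online appointments and how many face-to-face appointments they have had with their therapist in the past month".

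The paragraph then ends: "At T2, the average percentage of online and face-to-face appointments over the duration of the intervention will be calculated based on both measures".

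Table 1 and the *Caregivers* part of *Monthly assessments* both label the caregiver items as direct treatment time. The Discussion says that percentages of online direct treatment time will be calculated every three months to monitor adherence.

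**The concern.** The closing sentence changes the unit from time to appointments and applies the change to both sources. Read literally, it converts even the therapist registration, which is held in time, into an appointment percentage. The result would be set against limits of 50% and 10% that are defined in time.

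The two units agree only if online and face-to-face appointments have the same average length and no online time falls outside appointments. Phone calls and text messages count as online treatment, so equal length cannot be taken for granted. eHealth is online time in FASTb but need not involve an appointment.

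At stake is the check on whether the arms received the online shares that define them. The Background says that treatment integrity is key because a non-significant result may reflect poor implementation. The trial's hypothesis is equal effectiveness, so poor separation of the arms would tend to produce the expected result. Adherence is also listed among the treatment characteristics to be tested as moderators, where a change of unit changes the variable itself.

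**Working it through.** The article derives no figure from the 50% and 10% limits, so there is nothing to reproduce. The check compares the units and then illustrates the size of the gap.

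**Units side by side**

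| Place in the protocol article | Unit |
|---|---|
| Background (blended care), *FASTb-condition*, *FASTr-condition* | time |
| Abstract | contacts |
| *Treatment characteristics*, adherence paragraph, opening | time |
| Same paragraph, therapist source | time, coded online or face-to-face |
| Same paragraph, caregiver source | number of appointments |
| Same paragraph, closing sentence | appointments, from both sources |
| *Monthly assessments – Caregivers* and Table 1, label of the caregiver items | time |
| Discussion, three-monthly monitoring | time |

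The caregiver items have no described duration, so their counts cannot be turned into time.

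**Effect of appointment length**

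Let t be the true online share of time and r the mean length of an online appointment divided by the mean length of a face-to-face one. Without eHealth, the online share of appointments is

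q = (t/r) / [(t/r) + (1 − t)].

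For r = 0.5:

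- t = 0.50: 1.0 / (1.0 + 0.5) = 66.7%
- t = 0.10: 0.2 / (0.2 + 0.9) = 18.2%

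In the other direction, an appointment share of 50% corresponds to a time share of r/(1 + r). For r = 0.5 this is 0.5/1.5 = 33.3%.

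| r (assumed) | true 50% of time reads as | true 10% of time reads as | 50% of appointments is, in time |
|---|---|---|---|
| 1 | 50.0% | 10.0% | 50.0% |
| 0.75 | 57.1% | 12.9% | 42.9% |
| 0.5 | 66.7% | 18.2% | 33.3% |
| 0.25 | 80.0% | 30.8% | 20.0% |

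**Effect of eHealth that caregivers do not count (FASTb only)**

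Let e be the share of direct time spent on eHealth, with r = 1. A family at exactly 50% online time then shows an appointment share of (0.5 − e)/(1 − e):

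- e = 0.1: 0.4/0.9 = 44.4%
- e = 0.2: 0.3/0.8 = 37.5%
- e = 0.3: 0.2/0.7 = 28.6%

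This error runs opposite to the one from short online appointments, so the two can offset each other or either can dominate.

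**Invented weekly schedules**

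- FASTr, two 90-minute visits and one 15-minute call. The visits total 180 minutes, in line with the statement that "FASTr includes around 3 hours of face-to-face direct treatment time weekly". Time: 15/195 = 7.7%. Appointments: 1/3 = 33.3%.
- FASTb, one 90-minute visit and two 30-minute calls. Time: 60/150 = 40.0%. Appointments: 2/3 = 66.7%.
- FASTb, two 60-minute visits, one 60-minute video call and 60 minutes of eHealth. Time: 120/240 = 50.0%. Appointments: 1/3 = 33.3%.

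In each case the two scales give different answers to whether the limit is met. The first two schedules assume that caregivers report a short call as an appointment.

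**The case against.** The strongest reply is that the adherence paragraph must be read as a whole. It defines adherence in time, its first source is registered time, and Table 1 lists that registration as its own entry. The caregiver count is introduced as an addition. On this view the last sentence is a slip in wording, and the Abstract's term is only summary language. Much of this stands: the time-based measure is already planned. But the closing sentence is the one that states how the T2 score is computed, and it names both sources. The caregiver items are also labelled as time in two other places, so the slip is not isolated.

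A reader might infer more than the article supports, in four ways.

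- *Families will be put on the wrong side of the limits.* No rule classes or excludes a family at 50% or 10%. The planned analyses are by intention to treat and in completers, and completion is coded as positive or negative, not by online share.
- *Arms that failed to differ could go unnoticed behind a finding of equal effectiveness.* The therapist registration and the three-monthly checks are in time and would show it. Online share is also not the only designed difference: Table 2 excludes eHealth and the GRIP-app from FASTr and makes aftercare in FASTb online unless face-to-face contact is needed.
- *The eHealth gap is established and affects both limits.* It is inferred from the wording about appointments with the therapist, since the items are not printed. It can bear only on the FASTb limit, because FASTr uses no eHealth. The article does not say whether therapist registration captures eHealth time.
- *The juvenile's own sessions go uncounted.* The juvenile's monthly list has no contact item, but sessions with a therapist would fall under the therapist registration.

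It is also fair to say that every magnitude rests on assumed session lengths. Video calls may last as long as visits.

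**Conclusion.** The point holds as an internal contradiction. The arms and the opening of the adherence paragraph use share of time; the sentence that sets the T2 score uses share of appointments; and one of its two sources cannot be expressed in time. This needs no assumption.

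The size cannot be fixed from the article. Over assumed length ratios from 0.75 to 0.25, a true 50% reads as 57% to 80% and a true 10% as 13% to 31%. Uncounted eHealth at 10% to 30% of time would instead pull a true 50% in FASTb down to between 44% and 29%. At a ratio of 1 with no eHealth there is no discrepancy.

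The consequence is limited to the adherence check and to adherence as a treatment-characteristic moderator. The effectiveness analyses, the outcomes and the sample size are not touched. It is worth correcting because the closing sentence, followed literally, yields a score that cannot be compared with the limits it is meant to check.

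**What to change.** 1. Rewrite the closing sentence of the adherence paragraph under *Treatment characteristics*. Adherence to the 50% and 10% limits should be scored only as online direct treatment time divided by total direct treatment time, from the coded therapist registration.
2. Add a statement there of how eHealth time enters that percentage.
3. Report the caregiver appointment percentage as a separate supporting measure that is not compared with the limits.
4. Correct the label of the caregiver items in Table 1 and under *Monthly assessments – Caregivers*, so that they are described as appointment counts. Bring the Abstract's wording into line with the unit used in the Methods.

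The time score needs no new data collection, since the time is already registered and coded. The cost is a few edited sentences and a decision on eHealth. Rewording the caregiver items to ask for hours, or extracting eHealth platform logs, is optional. Hours are harder to recall than counts, a change during the trial would leave the caregiver series in two units, and the article does not say that logged platform time equals direct treatment time.

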### Aims of the study

The current study protocol describes an RCT comparing the effectiveness of FASTb and FASTr in the treatment of juveniles with antisocial behavior and their families. In addition, we will investigate the mechanisms of change of FASTb and FASTr, and for whom and under which conditions FASTb and FASTr work best. Thereby, new innovative steps will be taken to possibly improve the effectiveness and quality of mental health care for juveniles with antisocial behavior.

To this end, the aims of this study are threefold. The first aim is to compare the effectiveness of FASTb and FASTr in terms of reducing externalizing behavior, delinquency, out of home placement, and recidivism (risk) (primary treatment goals), and in terms of reducing substance use, contact with deviant peers, and in reaching client formulated goals (secondary treatment goals). It is expected that FASTb and FASTr are equally effective in reaching the primary and secondary goals of FAST. The second aim is to identify potential mechanisms of change in FASTb and FASTr. It will be investigated whether FASTb and FASTr, conform program theory, positively affect the intermediate outcomes: social support, family functioning (i.e., caregiver-juvenile conflict, caregiver-juvenile relationship quality, caregiver behavior, and caregiver competence), and cognitive distortions [6]. It is expected that these factors mediate the effectiveness of FASTb and FASTr. The third aim is to investigate what program and participant characteristics moderate FASTb and FASTr effectiveness. In other words, we aim to determine which families benefit most from FASTb and FASTr, and under which conditions. It is expected that the effectiveness of FASTb and FASTr is moderated by client factors (demographics such as gender and age, juvenile and caregiver psychopathology, and social support) and treatment characteristics (treatment integrity, treatment duration, intensity and completion, therapist-client alliance, motivation, expectancies, and cooperation). See Fig. 1 for a conceptual model of the research design.

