#### Moderation

The research questions related to the moderators (demographics, juvenile and caregiver psychopathology, social support, and treatment characteristics) will be answered by including an interaction term (moderator*condition) to the model with a correction for multiple testing. Post-hoc analyses for moderator effects will be conducted by splitting the file according to the moderator and again conducting an ANCOVA and calculating effect sizes separately for each group. Regression analyses will be conducted for the continuous moderators, and multi-group analyses will be performed for dichotomous variables.

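### The therapist expectancy item is scored relative to the assigned arm, so the planned moderator-by-condition test shows allegiance only as a main effect and can turn a prognostic belief into a false interaction

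*Protocol article*

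**What the plan says.** The Measures section of the Protocol article (Moderators, Treatment characteristics) describes "therapist report at T1 and T2 on one item asking how effective they think the assigned version of FAST (FASTb or FASTr) is" relative to the other version. Therapists answer at T1 and T2 on five points, with the low end meaning much less effective and the high end much more effective. Only the end points are labelled.

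The Aims section expects effectiveness to be moderated by "treatment characteristics (treatment integrity, treatment duration, intensity and completion, therapist-client alliance, motivation, expectancies, and cooperation", among others, so this item is a moderator under the third aim.

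Under Plan of data analysis, Moderation, the moderator questions are answered by "including an interaction term (moderator*condition) to the model with a correction for multiple testing". The post-hoc step is "splitting the file according to the moderator and again conducting an ANCOVA", with an effect size for each part. The same paragraph assigns continuous moderators to regression.

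The Procedure section says that families are randomised 1:1 and that the result is shared with the therapist. T1 falls before or during the first weeks of the intervention. The article nowhere reverses the score in one arm or recodes it to a common direction.

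**The concern.** A moderator-by-condition term can be interpreted only if a given moderator value means the same thing in both arms. Here it does not. A therapist firmly convinced that blended care is better scores 5 for a FASTb family and 1 for a FASTr family. Grouping families by this score therefore groups opposite beliefs.

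This matters for the third aim. The allocation is disclosed to therapists, so their belief in the version they deliver is a plausible influence on outcome. The Discussion says that moderator results can support targeted implementation of one version or the other. A missed or artificial expectancy finding would feed into that advice.

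**Working it through.** **Inputs from the article.** The item wording and 1–5 scale (Treatment characteristics); the interaction test and file split (Moderation); 1:1 randomisation of families (Procedure); alpha 0.05, N = 200 and drop-out of about 20% (Sample size calculation), which leaves 200 × (1 − 0.20) = 160. Sidedness is not stated; two-sided is used.

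**Assumed, not in the article.** A neutral midpoint of 3, belief SD of about 1 point, residual SD 1, slopes of 0.2 and 0.3 SD per point, no treatment effect, and independent families.

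**Step 1: the score.** Let b (−2 to +2) be belief in favour of FASTb, and C = 1 for FASTb, 0 for FASTr. The item as worded gives S − 3 = (2C − 1)b. At b = +2, S = 5 in FASTb and S = 1 in FASTr. Only the neutral answer scores the same in both arms.

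**Step 2: allegiance.** Suppose outcome improves by g per point of belief in the delivered version:

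Y = a + τC + g(S − 3) = a + τC − gb + 2g·bC.

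In terms of S there is one common slope g and the S × C coefficient is exactly 0. In terms of b, the arm difference changes by 2g per point. A noise-free fit with g = 0.3 and condition centred gives S main effect 0.3 and S × C 0.0. On the common scale it gives b main effect 0.0 and b × C 0.6, which is 2 × 0.3.

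**Step 3: belief that is only prognostic.** Suppose outcome depends on b equally in both arms, for instance because belief goes with therapist skill. Since (2C − 1)² = 1, b = (2C − 1)(S − 3), and with slope k:

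Y = a + τC + kb = a + τC − k(S − 3) + 2k·C(S − 3).

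Nothing is moderated, yet the S × C coefficient is 2k. With condition centred, recoding swaps the main effect and the interaction.

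**Step 4: rejection rates of the interaction test** (4,000 simulated trials per setting):

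| True mechanism | Slope | N | As scored | Recoded |
|---|---|---|---|---|
| Allegiance | 0.2 | 160 | 5.1% | 71.6% |
| Allegiance | 0.2 | 200 | 4.5% | 79.8% |
| Allegiance | 0.3 | 160 | 4.7% | 96.3% |
| Allegiance | 0.3 | 200 | 5.2% | 98.6% |
| Prognostic only | 0.2 | 160 | 70.4% | 5.8% |
| Prognostic only | 0.2 | 200 | 79.4% | 5.0% |
| Prognostic only | 0.3 | 160 | 96.0% | 5.0% |
| Prognostic only | 0.3 | 200 | 98.8% | 5.2% |

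In the allegiance rows, the main effect of S in the model as scored is significant exactly as often as the recoded interaction (71.6% and 79.8% at slope 0.2).

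**Step 5: file split.** Among families with S > 3, the FASTb families have pro-FASTb therapists and the FASTr families pro-FASTr therapists; for S < 3 this reverses. With prognostic belief and a true effect of zero, the FASTb minus FASTr difference is about +0.49 SD for S > 3 and −0.48 SD for S < 3 at slope 0.2. At slope 0.3 it is about +0.73 and −0.73 SD. The size is 2k times the mean distance of belief from neutral: 0.49 / (2 × 0.2) ≈ 1.22 points, and 2 × 0.3 × 1.22 ≈ 0.73. Under pure allegiance with beliefs centred on neutral, both parts show about 0.

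**The case against.** The strongest defence concerns the construct. The Background links better outcomes to higher expectancies about the treatment received, and belief in the assigned version is a fair measure of that. Allegiance to one mode of delivery is not a named research question. This stands as far as the main effect of the score is concerned. It does not rescue the interaction, which is the term the article uses to answer moderator questions.

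Second, a recode is variable derivation and could sit in an analysis plan not shown here. That is possible, and if so it need only be stated. But the article itself fixes the wording, the scale and the test, and these together mislead if followed as written.

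Several stronger readings are tempting but unsupported:

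- **A reader might infer that allegiance cannot be detected at all.** It remains visible as the main effect of the score in the same model.
- **A reader might infer that the split necessarily breaks the randomised comparison.** A five-point item treated as continuous may never be split, and the split biases the arm comparison only if belief is related to prognosis or therapist skill.
- **A reader might infer that a uniform lean among therapists makes only this scoring unusable.** If every therapist had b = 1, the recoded score would be constant and its interaction equally inestimable.
- **A reader might infer from the Background's remark on disappointing implementation that these therapists oppose blended care.** The remark concerns forensic care generally, and the same sentence says that therapists saw potential in it.

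**Conclusion.** The point holds for this item and the test as written. The opposite scoring, the zero interaction under pure allegiance and the interaction of 2k under pure prognosis are algebraic. They need only a neutral midpoint of 3 and linear effects, with no assumed effect size.

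The rates are illustrative. About 5% against 72–80% under allegiance, and 70–79% false interactions under prognosis, rest on the assumed slope of 0.2 SD per point and belief SD of about 1. They ignore the multiplicity correction that the article plans and the clustering of families within therapists, so 80% should not be read as the power the trial would have.

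The scope is one item under the third aim. The primary comparison and the caregiver PETS, which is not described as relative to the other arm, are unaffected. It should be corrected before the moderator analysis but does not threaten the trial's main result.

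**What to change.** 1. Before forming the interaction or any split, recode the T1 item to FASTb relative to FASTr for every family: keep the score in FASTb and use 6 minus the score in FASTr.
2. Report the main effect of the arm-relative score separately, as the effect of believing in the delivered version. Centre condition for this; with 0/1 coding the lower-order term is the slope in one arm only.
3. Do not use the T2 rating as a moderator. It follows treatment and may reflect the outcome.
4. For families still to be enrolled, preferably ask the item in the fixed direction and have the therapist answer before the allocation is disclosed.

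The cost is one recode and, for new families, one reworded item with a small change in timing. The recode does not remove any influence that knowing the arm had on answers already given. If therapists tended to endorse whatever was assigned, the recoded score still carries that, and the report should say so.
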